# Glossary of Abbreviations

| COVID-19 | Coronavirus-19 |
| --- | --- |
| EHR | Electronic Health Records |
| EMIS | Egerton Medical Information System – A provider of GP EHRs |
| GP | General Practitioner |
| TPP | The Phoenix Partnership – A provider of GP EHRs |

# Study Summary

| **TITLE** | How has the COVID-19 pandemic impacted the need for targeted weight management interventions amongst adults in the UK? An evaluation of pandemic-associated changes in BMI and metabolic parameters. |
| --- | --- |
| **DESIGN** | Secondary analysis of routinely collected electronic health records |
| **AIMS** | To evaluate, amongst adults living in the UK, how trends in measures of healthy weight (such as Body Mass Index) and metabolic risk factors (such as blood pressure (BP), blood lipid profiles, chronic blood glucose levels measured by Haemoglobin A1c (HbA1c) and smoking status) have changed since the onset of the COVID-19 pandemic using data in routinely collected GP electronic health records (EHRs) |
| **OUTCOME MEASURES** | Data on the following outcomes will be evaluated to compare values and trends in the period before and after the onset of the COVID-19 pandemic.   1. Body Mass Index - (to be calculated from most height and weight and/or measures independently entered as BMI). 2. Height to derive BMI – most recent adult height will be used, even if this was recorded prior to the study period. 3. Weight – all weights during the study periods will be recorded. 4. Systolic and Diastolic Blood Pressure (Home and Clinic readings). 5. Lipid profile: Total cholesterol, LDL cholesterol, HDL cholesterol, triglycerides 6. HbA1c 7. Smoking status 8. Referral to a weight management programme |
| **POPULATION** | All adults living in the UK and registered with a GP using electronic health records provided by The Phoenix Partnership (TPP) or Egerton Medical Information System (EMIS) on the 1^st^ March 2020. |
| **duration** | Routine data will be collected over the following time periods:  Pre-COVID: 1st March 2015 – 1^st^ March 2020  Post-COVID: 1^st^ March 2020 to the point of data analysis |
|  |  |

# INTRODUCTION

This analysis will investigate how the coronavirus pandemic has impacted the weight and metabolic risk factors of adults living in the UK and which groups have experienced the greatest change. This will identify specific groups of people that should be targeted by NHS-provided weight loss interventions following the onset of the coronavirus pandemic.

Lockdowns, stay at home orders and social distancing guidelines have had an impact on the lifestyles of people living in the UK. Studies have shown a reduction in physical activity during the pandemic, using a variety of data sources such as smartphone apps (McCarthy, Potts et al. 2021), recordings from implantable cardiac devices (Taylor, Ndiaye et al. 2021) and surveys. (Hillyard, Sinclair et al. 2021) Some international surveys have reported that lifestyle changes during the pandemic have resulted in weight gain and increased Body Mass Index (BMI) (a measure of if you are a healthy weight for your height)(Urzeala, Duclos et al. 2021). In the UK people joining the NHS Diabetes Prevention Program, a targeted intervention for people at high risk of diabetes, in the year following the pandemic were on average heavier than those who joined the programme in the years before the pandemic.(Valabhji, Barron et al.) But there is a lack of data on how the weight (and consequently BMI) of the general population of adults living in the UK has changed since the onset of the pandemic.

Even prior to the pandemic, obesity was common in the UK. The 2019 Health Survey for England (NHS Digital Lifestyles Team 2020) demonstrated that 64% of adults were overweight or obese. A study looking at wights measured in routinely collected GP records between 1998 and 2016 showed that a large proportion of adults moved from a ‘healthy weight’ to ‘overweight’ over a ten year period. (Katsoulis, Lai et al.) Obesity has long been known to be a risk factor for the development of a range of conditions such as diabetes, heart disease and stroke. This can be through the effect of obesity on established markers of metabolic risk such as: blood pressure (BP), blood lipid profile, and chronic levels measured by Haemoglobin A1c (HbA1c). Furthermore, obesity, and conditions linked to obesity such as diabetes, have been shown to increase the risk of hospitalisation and/or death from COVID-19. (Williamson, Walker et al. 2020)

In response to these challenges the NHS has invested in a range of interventions to support weight loss. Such as the NHS England Digital Weight Management Programme (DWMP), which is currently available to help overweight and obese people living with diabetes and/or hypertension manage their weight. This analysis will look at how the number of people meeting the eligibility criteria for the DWMP has changed since the onset of the pandemic through assessing BMI changes in these groups. We will also describe, amongst all adults living in the UK, how BMI and metabolic markers have changed since the onset of the pandemic, in order to assess the need for weight loss interventions in the overall population.

We will further investigate whether some groups of people have, since the onset of the pandemic, experienced more weight gain (and resultant increase in BMI) and/or worsening of their metabolic markers than others. These groups will be identified based on personal characteristics (such as age, sex, ethnicity, deprivation and/or region of residence) and whether they have another co-existent medical condition, such as asthma or chronic kidney disease. This will demonstrate specific population groups that may most benefit from targeted weight loss interventions. We will specifically look at co-existing medical conditions that have been deemed common and important by the NHS Qualify Outcome Framework (QOF) - a tool that is used to assess the quality of care provided by GPs. (National Institute for Health and Care Excellence)

The findings of this analysis will help inform NHS England health care policy around the extent of need for specific weight loss interventions and which specific groups are at greatest need of these interventions. As such this study answers important questions about the impact of the COVID pandemic on the health of the population and provides important data that will guide NHS service recovery. We have worked closely with key stakeholders, including the NHS England Clinical Director for Diabetes and Obesity, to develop a research project that answers clinically relevant research questions that can inform evidence based planning of interventions.

There is, to our knowledge, no available data answering these question. The analysis will be conducted through the OpenSAFELY platform which allows near real time access to routine electronic health records (EHRs) across over 98% of adults registered with a GP in the UK (further details of this platform are provided elsewhere in this application). As such this platform allows a more robust and complete analysis of UK health data than is currently available through any other platform or research database.

# STUDY OBJECTIVES

Aim: To evaluate, amongst adults living in the UK, how measures of healthy weight (such as Body Mass Index) and metabolic risk factors (such as blood pressure (BP), blood lipid profiles, chronic blood glucose levels measured by Haemoglobin A1c (HbA1c) and smoking status) have changed since the onset of the COVID-19 pandemic using data in routinely collected GP electronic health records (EHRs)

Objectives:

**Objective 1:** To investigate whether some groups of people have, since the onset of the pandemic, experienced more weight gain (and resultant increase in BMI) and/or worsening of their metabolic risk factors than others based on:

1. their personal characteristics (such as age, sex, ethnicity, deprivation and/or region of residence)
2. whether they are living with a chronic disease such as asthma, diabetes or chronic kidney disease have experienced more weight gain and worsening of their metabolic markers. Specifically considering the chronic diseases deemed common and important in the NHS Quality Outcomes Framework – a tool used to assess the quality of care provided by GPs.

**Objective 2:** To evaluate how the COVID-19 pandemic has affected the number of adults living in the UK eligible for targeted weight loss interventions, such as the [NHS Digital Weight Management Programme](https://www.england.nhs.uk/digital-weight-management/) (which is currently accessible to individuals with Diabetes or Hypertension and a BMI> 30 (or BMI > 27.5 for Black, Asian or Ethnic Minority backgrounds due to their increased risk of disease at a lower BMI)).

**Objective 3:** To identify which populations, based on demographic data and comorbidities, have experienced the greatest increase in weight and/or have the highest prevalence of obesity and should thus be targeted for weight loss interventions in the initial period of service restoration.

**Objective 4:** To assess the number of referrals to established weight loss programmes and whether there is a difference between groups of people on whether they are likely to be referred based on (i) the personal characteristics listed in Objective 1 above; and (ii) whether they are living with the chronic diseases discussed in Objective 1 above.

# Method

This will be a population based cohort analysis. Patients will be followed from 1^st^ March 2015 (5 years before the onset of the pandemic) till the point of data analysis, to evaluate how trends in BMI and metabolic markers have changed since the onset of the COVID-19 pandemic (1^st^ March 2020).

## Data Source: OpenSAFELY

We will use data from general practice (GP) records, obtained from the Electronic Health Record Providers, The Phoenix Partnership (TPP) and Egerton Medical Information System (EMIS), who provide GPs with the software and platform to create and store EHRs. Over 98% of patients in the UK registered with a GP have their primary care records stored through one of these providers. Data from the Hospital Episode Statistics will also be used to get further information on ethnicity, which can be poorly recorded in the primary care record.

All data will be accessed, linked and analysed through the OpenSAFELY platform - a new data analytics platform created to address urgent questions related to the Coronavirus Pandemic.

OpenSAFELY software, in the form of OpenSAFELY-TPP and OpenSAFELY-EMIS is hosted in the secure data environments of TPP and EMIS respectively. OpenSAFELY provides a secure software interface that allows NHS records to be pseudonymised, linked and analysed in near real-time; the GP patient data held never leaves the secure data environment of TPP or EMIS; other datasets are linked to it. TPP and EMIS , are Tier 3 data centres, accredited to NHS Digital standards for centrally hosted clinical systems (ISO 27001 standard and IG Toolkit version 2).

The OpenSAFELY platform allows researchers to develop analytical code using dummy data that has the same structure as the real data, but does not contain any real patient information. Once code related to data management and analysis has been developed it is run by the OpenSAFELY team in the OpenSAFELY-EMIS and OpenSAFELY-TPP. The researcher is then able to access aggregate outputs in the form of tables and charts without having access the real patient data. All outputs are checked for disclosure risks prior to release from the OpenSAFELY platform to the wider research group.

The OpenSAFELY model, allows the research team to perform an analysis of routinely collected data, without any access to the original source data.

## Study Population

Population size: The OpenSAFELY platform provides access to all patients registered with a GP surgery using TPP or EMIS Electronic Health Record software. A recent analysis in the OpenSAFELY platform demonstrated that gave access to 58 million patient records.(Walker, MacKenna et al. 2021)

Inclusion Criteria

1. Registration with a GP surgery, on the 1^st^ March 2020, that uses EMIS or TPP software to record and store electronic health records
2. All adults: aged >18 and <110 on the 1^st^ March 2020
3. Recorded female or male sex on the 1^st^ March 2020

Exclusion Criteria

1. Patients will less than 12 months primary care data available on the 1^st^ March 2020

(new registrations in the 12 months prior to 1^st^ March 2020 will be excluded from the analysis as there are often delays in the transfer of health records between practices).

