## Study Measures

**Study Outcomes**

This analysis will evaluate how the values and trends in the following outcomes changed since the onset of the COVID-19 pandemic:

1. Body Mass Index - (to be calculated from most height and weight and/or measures independently entered as BMI).
2. Height to derive BMI – most recent adult height will be used, even if this was recorded prior to the study period.
3. Weight – all weights during the study periods will be recorded.
4. Systolic and Diastolic Blood Pressure (Home and Clinic readings).
5. Lipid profile: Total cholesterol, LDL cholesterol, HDL cholesterol, triglycerides
6. HbA1c
7. Smoking status
8. Referral to a weight management programme

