**Covariates**

Stratified analysis will be undertaken to assess the impact of the COVID pandemic based on variations in the following:

1. Age
2. Sex
3. Ethnicity recorded in primary care records or linked HES data.
4. Index of Multiple Deprivation (IMD)
5. Geographic Data
6. The presence of Comorbidities - existing and new diagnoses of Quality Outcomes Framework (QOF) conditions
   1. Atrial Fibrillation
   2. Coronary Heart Disease
   3. Heart Failure
   4. Hypertension
   5. Peripheral Arterial Disease
   6. Stroke and TIA
   7. Diabetes Mellitus
   8. Asthma
   9. Chronic Obstructive Pulmonary Disease
   10. Dementia
   11. Depression
   12. Mental Health
   13. Cancer
   14. Chronic Kidney Disease
   15. Epilepsy
   16. Learning Disabilities
   17. Osteoporosis
   18. Rheumatoid Arthritis
   19. Palliative Care
   20. Non diabetic hyperglycaemia
7. Date of registered live birth or still birth – to identify outcome data in the prenatal or postnatal periods which should be excluded from the analysis.

QOF conditions *have been included as a covariate, to identify whether patients living with specific comorbidities such have experienced greater need for targeted weight loss interventions. We have chosen to look at comorbidities covered by QOF as these have been benchmarked as common and/or important by NICE, and are likely to be well-coded in the EHR.*

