## Study Duration

Outcome data will be collected over the following time periods:

Pre-covid period: 1^st^ March 2015- 1^st^ March 2020

This will be included to identify baseline levels of the outcomes in the population and underlying trends prior to the onset of the pandemic.

Post-covid period: 1^st^ March 2020 – point of data extraction

This will allow an assessment of how values and trends varied in the periods post covid compared to the pre-covid period

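### Adulthood is tested only on 1 March 2020 while outcomes run back to March 2015, so adolescent measurements, some paired with a later adult height, can enter the youngest group's pre-COVID baseline and trend.

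*Protocol*

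**What the plan says.** Four rules, all in the Protocol, bear on this point.

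- **Who is in** (Study Population, Inclusion Criteria): "All adults: aged >18 and <110 on the" 1 March 2020. Age is tested on that one date.
- **When outcomes are taken** (Method): patients are followed from 1 "March 2015 (5 years before the onset of the pandemic) till the point of data analysis". Study Duration gives the purpose of the five pre-COVID years: "This will be included to identify baseline levels of the outcomes in the population and underlying trends prior to the onset of the pandemic".
- **Which weights** (Study Outcomes, item 3): "Weight – all weights during the study periods will be recorded".
- **How BMI is formed** (Study Outcomes, items 1 and 2): "to be calculated from most height and weight and/or measures independently entered as BMI", and for height, "most recent adult height will be used, even if this was recorded prior to the study period".

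In item 2 the word adult qualifies the height; nothing equivalent qualifies the weight. The only exclusion of individual outcome records is the window of six months either side of a birth (Statistics and data analysis, item 10). Age is the first stratifier under Covariates, where "Stratified analysis will be undertaken to assess the impact of the COVID pandemic based on variations in the following", but neither the age bands nor the date on which age is taken is given. The stated aim concerns adults.

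**The concern.** The eligibility date is five years later than the start of outcome collection, so an adult at index need not have been an adult when measured. Followed literally, the rules admit adolescent records to a study of adults. For calculated BMI they also divide a weight taken before growth is complete by the square of a height reached later.

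Both effects act on the pre-COVID period in the youngest patients. Early BMIs are low, partly because of the height mismatch and partly because adolescents are still growing, so the pre-COVID slope is steeper than an adult trend. If that slope serves as the expected trend after March 2020, ordinary flattening in early adulthood could look like a slowdown and hide a real rise. Objective 1 compares groups by age, and Objective 3 uses group results to say who should be targeted, so a distorted youngest group would reach a stated output of the study.

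**Working it through.** The protocol gives no figure to reproduce here. The dates below come from the protocol. Heights, weights, age bands and recording rates are assumptions, because the protocol gives none.

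**1. Who is affected.** Age on 1 March 2015 = age on 1 March 2020 minus 5. Someone just over 18 at index was just over 13 (19 − 5 = 14 if >18 means 19 or more completed years). Pre-COVID time under 18 is 23 − a years for exact age a at index:

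| Exact age at index | Years under 18 | Share of the 5 years |
|---|---|---|
| 18 | 5 | 100% |
| 19 | 4 | 80% |
| 20 | 3 | 60% |
| 21 | 2 | 40% |
| 22 | 1 | 20% |
| 23 or over | 0 | 0% |

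**2. Dilution within a band** (assuming uniform ages, equal recording and bands set at index). Summing 23 − a over ages 18 to 23 gives 5 × 5 / 2 = 12.5. Divide by band width × 5:

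- 18-22: 12.5 / (5 × 5) = 50%
- 18-24: 12.5 / (7 × 5) = 36%
- 18-29: 12.5 / (12 × 5) = 21%
- 18-39: 12.5 / (22 × 5) = 11%

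If entry starts at 19, the sum is 4 × 4 / 2 = 8. The shares become 8 / (6 × 5) = 27% for 19-24 and 8 / (11 × 5) = 15% for 19-29.

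**3. Height mismatch, calculated BMI only.** Calculated BMI / true BMI = (height then / adult height)².

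- 90% of adult height: 0.90² = 0.81, so a true 20 becomes 16.2
- 95%: 0.95² = 0.90, so 20 becomes 18.1
- 99%: 0.99² = 0.98, so 20 becomes 19.6
- Growth complete: 1.00, no error

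As one assumed case, 45 kg at 1.57 m is 45 / 1.57² = 18.3. With an adult height of 1.68 m it becomes 45 / 1.68² = 15.9.

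**4. Slope.** Change in (weight / adult height²) over 5 years, for assumed growth paths:

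- 48 to 70 kg at 1.76 m: BMI 15.5 to 22.6, +1.42 per year
- 45 to 64 kg at 1.70 m: 19 / 1.70² / 5 = +1.31 per year
- 55 to 60 kg at 1.63 m: BMI 20.7 to 22.6, +0.38 per year

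**5. How much of the slope is the height error.** Take the middle path with a height of 1.57 m at the start. True BMI goes from 45 / 1.57² = 18.3 to 64 / 1.70² = 22.1, or +0.78 per year. So 0.78 / 1.31, about 60%, is real adolescent BMI change. The remaining 40% or so comes from dividing by a height not yet reached. Neither part is an adult trend.

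**The case against.** The best case on the other side has four parts.

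- **It is an omission that a SAP or the extraction code may fill.** The aim is limited to adults, the authors wrote adult height, and the SAP is not shown. This stands to the extent that one cannot say such records will be analysed. But an age filter elsewhere would narrow the protocol's own rule that "all weights during the study periods will be recorded", and the protocol already states a record-level exclusion where body weight is not comparable (around births). Its text should agree with any such filter.
- **The height error is not general.** BMIs entered directly avoid the mismatch, and a person with no adult height on record gets no calculated BMI. This stands. A reader might infer that every childhood BMI in the data would be falsely low; the protocol does not support that.
- **The harm depends on choices not stated.** It needs age bands set at index, a pre-COVID slope projected forward, and adolescents measured often enough to matter. Age standardisation could even give under-18 records no weight, if age is taken at measurement against an adult standard. This stands too. A reader might infer that the youngest band's result is wrong by construction; with model, bands and recording frequency unspecified, that does not follow.
- **A 13-year-old is the extreme.** Someone aged exactly 22 at index contributes at most one under-18 year, near or at full height. This bounds the size but does not change the direction.

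**Conclusion.** The point holds as a defect in the rules as written. Eligibility by age on 1 March 2020, outcomes from 1 March 2015 and adult height for every calculated BMI together admit under-18 measurements from anyone under 23 at index.

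The error in a calculated BMI is about 10% at 95% of adult height, 2% at 99% and nil once growth is complete. Directly entered BMI, blood pressure, lipids, HbA1c and smoking status carry no height error but are still non-adult values. The bias is confined to the youngest group and diluted in the all-adult series. The 36% (18-24) and 21% (18-29) shares rest on uniform ages and equal recording.

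The expected direction is a steeper pre-COVID slope, which could mask a rise after March 2020 if that slope is the expected trend. The illustrated slopes of +0.38 to +1.42 per year rest on assumed heights and weights and should not be read as estimates of bias in this study, still less as wholly a height artefact.

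**What to change.** Before extraction, amend Study Population and Study Outcomes as follows.

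- Use only outcome records dated on or after the patient's 18th birthday.
- Calculate BMI only from a weight and a height both recorded at age 18 or over.
- Define age bands by age at measurement. The March 2015 data for an 18-24 band then come from people aged 23-29 at index (18 + 5 to 24 + 5), so the youngest band keeps an adult pre-COVID series.
- Reconcile >18 with the intention to include all adults: read in completed years, it drops 18-year-olds.

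**Cost.** One date filter and a few words. At exact ages 18, 19, 20, 21 and 22 at index, people lose 5, 4, 3, 2 and 1 years of their own pre-COVID window; those aged 23 or over lose nothing. Some interpretable records go too, such as smoking status or HbA1c at 17. Individual-level change in the very youngest will have little or no pre-COVID baseline, and the report should say so. The cohort is also closed at index, so with bands by age at measurement no new 18-year-olds enter after March 2020 (two years on, the youngest are 18 + 2 = 20). Age should therefore be standardised within the youngest band.

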# STATISTICs and data analysis

1. Primary care data is entered by health care professionals into the Electronic Health Records (EHRs) as a combination of free text and clinical codes which specify specific diseases and disease processes. Best practice of record keeping is to ensure that clinical codes are entered in addition to free text so EHRs can be rapidly searched and reviewed for clinical, audit and research purposes. More than one code can be used to represent a single clinical condition or measurement, therefore ‘code lists’ are required to identify all the relevant information.
2. This analysis will be limited to data entered as clinical codes Specific code lists will be developed to identify data related to each of the study outcomes, exposures and covariates listed above. Where established code lists are available they will be reviewed and curated to ensure the data being collected are aligned with the specific analysis being performed. Such code lists may be available from previous studies researching the same conditions or aligned with care processes, such as the Quality Outcome Framework ( a national system of monitoring the quality of GP care processes in relation to common and important chronic diseases such as diabetes, hypertension and asthma).
3. Data will be analysed using STATA.
4. Descriptive statistics will be used to describe the numbers and character of the population who are having each of the outcome measures and how this varied in the period before and after the onset of the pandemic. This will help describe any bias introduced by different health care practices in the period before and after the pandemic in terms of which individuals were having the outcomes measures.
5. Changes in the values and trends of each of the outcomes listed above will be assess on a population level and individual level in time series analysis standardised for age and sex using an appropriate model based on the character of the data.
6. Further analyses will assess how population level trends in each of the outcomes have changed since the onset of the pandemic, after standardisation for age and sex, using an appropriate model based on the character of the data.
7. Multilevel modelling, accounting for clustering at the level of the Primary Care Network will be used to evaluate whether these outcomes varied by the demographic subgroups or comorbidities listed above.

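### Entry closes on 1 March 2020, the pre/post boundary, so the youngest attained-age band can show a BMI rise produced only by the cohort growing older

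*Protocol*

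**What the plan says.** All three eligibility rules in the protocol's Study Population section are tested on one date, 1 March 2020:

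- age: "All adults: aged >18 and <110 on the" that date;
- registration: "Registration with a GP surgery, on the" same date;
- prior records: the exclusion of "Patients will less than 12 months primary care data available on the" same date.

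No later route of entry is given. The Study Summary describes the population as "All adults living in the UK and registered with a GP using electronic health records", again tied to 1 March 2020.

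The Method section says "This will be a population based cohort analysis" and runs follow-up from 1 "March 2015 (5 years before the onset of the pandemic) till the point of data analysis". Study Exposures and Study Duration make 1 March 2020 the boundary for assessing "how values and trends varied in the periods post covid compared to the pre-covid period". The post-COVID period has no end date.

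Item 5 of the statistics section plans population-level and individual-level change "in time series analysis standardised for age and sex". The Covariates section lists age first among the stratifiers. The protocol does not say whether age means age at measurement or age on 1 March 2020, nor how wide the bands are.

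**The concern.** The date that closes the cohort is also the date of the interruption. Before it, people who turn 18 keep refilling the youngest adult ages, because anyone who was 18 at some point in 2015-2020 is old enough to qualify in March 2020. After it, nobody refills them. A band that starts at 18 then grows older from the inside, and BMI tends to rise with age in young adults, so its mean can drift upward from the assumed onset of the pandemic with no change at any given age.

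Objectives 1 and 3 compare groups for the greatest increase, in order to direct weight-loss services. A drift confined to one age stratum distorts that comparison. The protocol's section on risk of bias deals with who gets measured. It does not mention the ageing of a closed cohort, and the planned descriptive checks are not aimed at it.

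**Working it through.** The protocol gives no figure for this point, so there is nothing to reproduce. The check is cohort arithmetic.

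**Inputs from the protocol.** One eligibility date, 1 March 2020; five pre-COVID years from 1 March 2015; an open-ended post-COVID period.

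**Assumptions.** Ages are uniform within a band. BMI rises linearly by 0.1-0.4 kg/m2 per year of age. The Introduction supports only the direction, citing a study of adults moving up a weight category over ten years, and gives no slope. Post-COVID follow-up is 1-2 years, with 3 years shown for coverage. Coverage refers to the age rule alone.

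**Formula.** Let t be years from 1 March 2020. A person aged a at time t is in the cohort if a - t >= L, where L = 18 if >18 means exact age and L = 19 if it means completed years. For a band from b up to but not including U, the lowest age present is low = max(b, L + t). Coverage is (U - low)/(U - b), and mean age is (low + U)/2.

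**Band 18-24 (b = 18, U = 25), age at measurement, L = 18.**

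| t | low | coverage | mean age |
| --- | --- | --- | --- |
| -5 to 0 | 18 | 7/7 = 100% | 21.5 |
| 1 | 19 | 6/7 = 86% | 22.0 |
| 2 | 20 | 5/7 = 71% | 22.5 |
| 3 | 21 | 4/7 = 57% | 23.0 |

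**Apparent BMI rise with no true change** = (shift in mean age) x (slope):

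- 1 year: 0.5 x 0.1 to 0.5 x 0.4 = 0.05 to 0.20 kg/m2;
- 2 years: 1.0 x 0.1 to 1.0 x 0.4 = 0.10 to 0.40 kg/m2.

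A segmented regression on an 18-29 band (slope 0.3, 60 months before, 18 or 24 months after) gives no pre-trend, no level step and a false slope change of 0.5 x 0.3 = +0.15 kg/m2 per year at 1 March 2020.

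**Completed years, L = 19.** Depletion starts on 1 March 2019. At t = 0 the age-18 cell is already empty and the 18-24 band is at 6/7 = 86%, with mean age 22.0. At t = 2 it is at 4/7 = 57%, with mean age 23.0. The same segmented regression gives a pre-trend of +0.014 per year, a level step of +0.10 and a slope change of about +0.14 per year.

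**Single years of age at measurement, L = 18.** The age-18 cell is empty by March 2021. It becomes undefined; it does not drift upward over the years.

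**Age fixed at 1 March 2020.** No cell empties. In the 18-29 group mean attained age is 19 in 2015, 24 in 2020 and 26 in 2022, one year per year on both sides, so a linear age effect gives no break at the boundary. This counts all readings, including those of members who were only about 13-14 in March 2015. Each person's age group never changes, so standardisation removes none of this ageing.

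**All-age series.** If birth years are about equal, each is roughly 1.3% of adults (assumption) and 18-24 is 7 x 1.3% = about 9%. At 2 years, 0.09 x 0.10 to 0.09 x 0.40 = about 0.01 to 0.04 kg/m2.

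**After the fix.** With entry on reaching 18 in both periods, coverage stays at 100% and mean age stays constant, so the artefact is 0. It is also 0 when single years of age are compared only over ages covered in both periods.

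**The case against.** The strongest reply is that the false rise needs two choices the protocol has not made: age at measurement, and bands wider than one year starting near 18. Such details commonly belong in a statistical analysis plan, and none is shown here. That stands, and it makes the bias conditional. It does not dispose of the point, because the entry rule is fixed in the protocol and shapes the cohort query. A later plan could restrict the ages reported, but it could not recover people who were never extracted.

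Fixing eligibility at the exposure date is also a recognised cohort design, and within-person change, which item 5 also plans and which speaks directly to Objective 1, is not exposed to this mechanism. Both points stand. They limit the problem to the age-specific population-level series.

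A reader might infer that the youngest cells empty only after the pandemic date and that the study will therefore report weight gain in young adults. The documents do not support that. With age fixed at 1 March 2020 no cell empties, and with single years a cell becomes undefined. If >18 means completed years, depletion begins a year before the boundary. Nor can the loss of a whole birth year (about 1.3% of adults) be added to the figures for L = 18, because the two rest on different readings of >18. Read as exact age, the criterion drops essentially nobody aged 18 and may just be loose notation.

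**Conclusion.** The concern holds in conditional form. The protocol closes entry on the interruption date, and under attained-age bands wider than one year this can produce an apparent rise in the youngest band of about 0.05-0.20 kg/m2 at 1 year and 0.10-0.40 at 2 years. Those figures depend on the assumed slopes, uniform ages and follow-up length, none of which the protocol gives. Fixing age at 1 March 2020 avoids the emptying but leaves the cohort's ageing in the series. The all-age result moves very little. Because Objectives 1 and 3 rank groups by increase, the matter should be settled before the cohort is extracted. Confidence is medium, since the age definition and bands are open.

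**What to change.** For the population-level series, state that age is age at measurement, and adopt one of two rules:

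1. Let people enter on reaching 18 throughout both periods, up to extraction, under the same 12-month record rule.
2. Keep the cohort closed and compare, by single year or narrow band, only ages covered in both periods. With T post-COVID years this means ages 18 + T and over on the exact-age reading, for example 20 and over at 2 years. Report no population-level trend for younger ages.

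In either case write the lower age limit as 18 or over, so that it agrees with the description of the cohort as all adults.

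The cost is protocol wording and, for the first rule, a changed cohort query. Under the first rule later entrants have no adult pre-COVID data and count in population-level series only. Under the second, the youngest adults get no reported trend. The within-person analyses need no change on this account.
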